**Patient Care Implications:**

Suggested Regimen for Treatment of Hypersensitivity Reactions

Primary prophylaxis (1 hour to 30 minutes prior to BMS247550):

- H1 blocker (diphenhydramine 50 mg po or IV)

H2 blocker (ranitidine 150 mg po or 50 mg IV or another equivalent H2 blocker)

Treatment and secondary prophylaxis:

- CTC Grade I Allergic/Hypersensitivity Reaction (transient rash, drug fever < 38°C): Supervise without further treatment.
- CTC Grade 2 Allergic/Hypersensitivity Reaction (urticaria, drug fever greater than or equal to 38°C and/or asymptomatic bronchospasm): Interrupt the infusion. If symptoms abate, attempt re-infusion at a slower rate. If the symptoms recur, discontinue infusion and follow guidelines below.
- Recurrent CTC Grade 2 or CTC Grade 3 or 4 Allergic/Hypersensitivity Reactions: Stop the infusion. Administer additional doses of H1 and H2 blockers intravenously. Administer IV steroids (see discussion below) and consider epinephrine and bronchlodilators as clinically indicated. Further treatment should be delayed 24 hours. Prior to rechallenge and with all subsequent cycles, give both an H1 and H2 blocker intravenously plus dexamethasone 20 mg x 2 doses (orally or intravenously) 12 and 6 hours pre BMS247550. Dexamethasone could be used at the investigator’s discretion in subsequent cycles for recurrent (i.e. occurring despite slowing infusion as discussed above) grade 2 reactions but would not be mandated.

Note that the administration of dexamethasone immediately prior to BMS247550 is unlikely to be effective.

**Note:** An extensive description of the expected adverse events associated with BMS 247550 is provided in Section 5.1 and Appendix A.

##### 6.2 Availability

BMS 247550 is an investigational agent supplied to investigators by the Division of Cancer Treatment and Diagnosis (DCTD), NCI.

BMS 247550 is provided to the NCI under a Clinical Trials Agreement (CTA) between Bristol Myers Squibb and the DCTD, NCI (see Section 10.4).

**6.3 Agent Ordering**

Except in very unusual circumstances, each Participating Institution will order DCTD-supplied investigational agents directly from CTEP. Investigational agents may be ordered by a participating site only after the initial IRB approval for the site has been forwarded by the Coordinating Center to the CTEP PIO.

NCI-supplied agents may be requested by the Protocol Chair (or their authorized designees) at each Participating Institution. Pharmaceutical Management Branch (PMB) policy requires that the agent be shipped directly to the institution where the patient is to be treated. PMB does not permit the transfer of agents between institutions (unless prior approval from PMB is obtained). Completed Clinical Drug Requests (NIH-986) should be submitted to the PMB by [contact] or mailed to the Pharmaceutical Management Branch, CTEP, DCTD, NCI, [name], Bethesda, MD 20892.

**6.4 Agent Accountability**

The Investigator, or a responsible party designated by the investigator, must maintain a careful record of the inventory and disposition of all agents received from DCTD using the NCI Drug Accountability Record Form.

1. **CORRELATIVE/SPECIAL STUDIES**

Genomic DNA and total RNA will be extracted from both mouthwash specimens and PBMCs as a source of normal control cells, which we can utilize to evaluate the occurrence of polymorphisms in tubulin. Where tumor biopsies are available, nucleic acids will also be extracted for the purpose of mutational analysis of tubulin and RT-PCR analysis of additional genes.

1. To evaluate the % microtubule (MT) bundle formation in Peripheral Blood Mononuclear Cells (PBMCs), as a surrogate marker of drug pharmacodynamics.

The mechanism of action of Taxol involves mitotic arrest through microtubule stabilization, which is characterized by the formation of stable bundles or parallel arrays of microtubules and/or the formation of mitotic asters. Since BMS 247550 shares the same mechanism of action as Taxol, we will investigate its effects on the extent of microtubule bundle and mitotic aster formation in pre‑and post‑treatment PBMCs and tumor samples by immunohistochemistry utilizing an alpha‑tubulin antibody. These results will be correlated with pharmacological data at the Phase II dose. This will be important in validating any PK/PD relationships with this class of agent.

2. To determine whether polymorphisms or mutations in tubulin affect response, or toxicity to BMS 247550.

To further define the importance of both -tubulin isotype expression and frequency of mutations in Class I with clinical response to BMS 247550, we will isolate total RNA from patient tumors (when available) pre‑ (0h) and post‑ treatment (1 and 24h) (Appendix D). Samples will be reverse transcribed into cDNA's using random hexamers. Total protein will also be isolated from samples to correlate RNA and protein expression levels. All total RNA, cDNA and protein lysates will be carefully catalogued and stored at –70ºC. Using sequence‑specific primers that we havedesigned, -tubulin isotype cDNA expression levels will be evaluated by real time PCR and transcript levels accurately determined. In addition, the cDNA's from Class I ‑tubulin will be amplified using five nested‑primer sets and the products purified for automatic sequencing. At the Phase II dose of BMS 247550, the response in each patient will be correlated with (a) alterations in ‑tubulin isotype distribution, and (b) the occurrence of polymorphisms / mutations, initially in Class I isotypes. PBMCs and buccal cells (obtained pre-BMS 247550 treatment) will be used to control for naturally occurring polymorphisms in tubulin sequences, or for patients who have acquired tubulin aberrations due to previous chemotherapy.

3. To evaluate whether BMS 247550 efficacy / response is modulated by drug transporters, such as MDR1, MRP, and cMOAT.

Another mechanism for Taxol resistance is the overexpression of P-glyocoprotein. Taxol has a high degree of hydrophobicity and therefore is a substrate for P‑glycoprotein, the product of the MDR1 gene. The multidrug resistance-associated protein, MRP, is a member of the ABC transporter family of genes that regulates cellular drug efflux. Phenotypically, overexpression of MRP confers resistance to anthracyclines, vincristine and etoposide, but not to Taxol. Whilethe preliminary data for BMS 247550 suggests that it retains efficacy in models that overexpress P-glycoprotein, the possibility remains that this compound could induce the overexpression of alternate transporters, therefore contributing to acquired resistance39,60. Hence, tumor cells from all evaluable patients will be routinely screened for MDRI and MRP overexpression using RT‑PCR. We will also screen for expression of canalicular multispecific organic-anion transporter (cMOAT), a homologue of MRP whose function is to transport organic anions from hepatocytes into bile61. Increased expression of cMOAT has been reported in a variety of human cancer cell lines and in drug resistant cell lines61, particularly with cisplatin resistance62. It is anticipated that cMOAT will confer resistance to natural product anticancer drugs in a fashion similar to MRP, therefore it seems prudent to assess its expression in tumor cells by RT‑PCR.

4. To evaluate the cytotoxic / growth inhibitory characteristics of BMS 247550.

The mechanismby which Taxol induces cell death is not fully understood, and the role of proteins that regulate apoptosis (e.g. bel‑2 family members, p53, caspases) and modulate Taxol‑induced cytotoxicity requires clarification. The well documented effects of Taxol including microtubule bundle formation and mitotic arrest are not observed at low Taxol concentrations (10nM), although apoptosis is prevalent. It has been suggested that defects in apoptosis-regulating genes are important for the pathogenesis of human cancers65, a hypothesis that is supported by the observation that p53 is frequently deleted or mutated in various cancers. In support of this hypothesis, bcl‑2, an inhibitor of apoptosis is overexpressed in a variety of cancer types conferring a survival advantage to cancer cells66. Bcl‑2 and bcl‑x proteins prevent apoptosis by blocking cytochrome c release from the mitochondria, by either modulating the ionic imbalances in mitochondria or by binding to the apoptotic protease‑activating factor 1 (Apaf‑1) and preventing downstream caspase activation. Taxol has been shown to bind to bcl-2 inducing its inactivation by hyperphosphorylation and N-terminal cleavage to produce a pro-apoptotic protein that is unable to revert the death stimulus. Hyperphosphorylation of bc1‑2 has also been observed following exposure to other microtubule interacting drugs. We will evaluate theexpression of bcl‑2 and bcl-xin pre‑and post‑treatment tumors and PBMC samples using immunofluoresence and Western blotting techniques, taking note of any evidence ofhyperphosphorylation in post‑treatment tumor samples. We anticipate that hyperphosphorylation will be difficult to ascertain invivo since the activation of bcl-2 and bcl‑x is transient, and may be associated with mitotic arrest67. Moreover, we will correlate the degree of overexpression of both proteins with clinical outcome. We also plan to quantify the degree of drug-induced cell death in tumor samples pre- and post BMS 247550 administration for evaluable patients, utilizing an antibody that recognizes only the cleaved product of the nuclear repair enzyme PARP (Appendix E).

Other interesting proteins that regulate apoptosis are called inhibitors of apoptosis (IAPs), whose function are to prevent apoptosis by mechanisms involving inhibition of caspases, either directly or indirectly. Survivin is a member if the IAP family that is expressed at the G2/M phase of the cell cycle and associates with microtubules. Disruption of the surviving-microtubule interactions results in the loss of survivin's anti‑apoptotic function and increased caspase-3activity. Hence, survivin is thought to function as a regulator of the G2/M checkpoint, and itsoverexpression in human cancer cells may contribute to the aberrant progression of transformed cells through mitosis68. Since the mechanism of activation of BMS 247550 involves mitotic arrest, we will evaluate and compare the expression of survivin in pre‑and post‑treatment tumors using antibodies specific for survivin. In addition, we will assess the interaction of survivin with microtubules in these samples by immunoprecipitating with - or -tubulin prior to western blot analysis.

To evaluate the effect of BMS 247550 on cell cycle progression we will monitor the expression of mitotic markers, such as TG3 in tumor biopsies pre- and post-drug treatment.

5. To assess the effect of BMS 247550 on stathmin expression and phosphorylation status.

Stathmin, or p19, is a phosphorylation‑responsive regulator of microtubule dynamics that binds to and sequesters tubulin dimers, resulting in inhibition of microtubule assembly. We have previously shown that the microinjection of recombinant stathmin into COS-7 cells induces loss of microtubules63. The phosphorylation status of stathmin fluctuates during the cell cycle, reaching a maximum at mitosis, however the non‑phosphorylated form appears to be responsible, for microtubule destabilization. Our preliminary data indicate that stathmin inhibits the effects of Taxol in an *in vitro* microtubule assembly assay, and also in cells suggesting that endogenous levels of stathmin in human tumors may determine sensitivity to Taxol and possibly other microtubule interacting agents. Recent evidence suggests that Raf‑1 kinase associates with stathmin, and we have demonstrated that there is a dose and time‑dependent phosphorylation of stathmin following Taxol exposure64. The depletion of Raf‑1 kinase is associated with decreased Taxol‑induced stathmin phosphorylation levels, a phenomenon that may be partially mediated by MAP kinases. It is reasonable to assume that BMS 247550 will exert similar effects on stathmin and we anticipate that there may be a strong correlation between stathmin expression status and BMS 247550 efficacy. We will determine the expression status of stathmin in pre- and post-*­*treatment patient tumors using RT‑PCR to ascertain mRNA expression levels, and at the protein level, using specific antibodies which recognize either phosphorylated or non-phosphorylated epitopes and analyzing samples utilizing non‑denaturing electrophoresis (Appendix E). This information will be used to ascertainwhether endogenous stathmin expression correlates with clinical response to BMS 247550,or whether the distribution of phosphorylated and non‑phosphorylated stathmin is modulated following treatment. The storage of all tumor extracts at ‑70C will facilitate future expression studies of other microtubule‑associated proteins such as MAP4 and E-MAP-115, both of which regulate microtubule dynamics.

6. To correlate progression through G2 and mitosis with response to BMS 247550:

Phosphorylation of histone (H3) correlates with chromatin condensation at mitosis. A new monoclonal antibody (anti-H3-P) was developed that recognizes phosphorylated H3 (H3-P). Mitotic cells, from prophase to telephase, reacted with anti-H3-P. The analysis of phosphorylation of H3 before and afterBMS-247550, when combined with multi-parameter analysis of cycle position and expression of other proteins offer new possibilities to study molecular mechanisms associated with the G2 to M transition and chromatin condensation. In addition, we will examine pre- and post-treatment available tissues for mitotic phosphorylation recognized by the antibody MPM2.

**NYU 00-57 STUDY CALENDAR**

Baseline evaluations are to be conducted no more than 1 week prior to administration of study agent. Scans and x-rays must be done no more than 4 weeks prior to the start of therapy. If the patient’s condition is deteriorating, laboratory evaluations should be repeated no more than 48 hours prior to initiation of the next cycle of therapy.

|  | **Pre-Study** | **Each cycle** | | **Every 2 cycles** | **Off Study** |
| --- | --- | --- | --- | --- | --- |
| **D1, D8, D15** | **Prior to next cycle (D22-27)** |
| BMS 247550 |  | X |  |  |  |
| **Informed consent** | X |  |  |  |  |
| **Demographics** | X |  |  |  |  |
| **Medical history** | X |  | X |  |  |
| **Physical exam** | X |  | X |  |  |
| **Vital signs** | X | X |  |  |  |
| **Height / Weight** | X | X |  |  |  |
| **Medications** | X |  | X |  |  |
| **Performance status** | X |  | X |  | X |
| **Hb, ANC, plts*** | X | X | X |  |  |
| **Serum chemistry**** | X |  | X |  |  |
| **EKG (as indicated)** | X |  |  |  |  |
| **B-HCG** | X |  |  |  |  |
| **Adverse Events** |  | X | X |  | X |
| **Tumor Measurements** |  |  |  | X |  |
| **Collection of PBPC’s (1 & 24h: cycles 1 &2)** | X | X |  |  |  |
| **Tumor Biopsy (1 & 24h cycles 1 &2)** | X | X |  |  | X |

* If a patient develops Grade 4 neutropenia, CBC’s will be checked 3 times per week until resolution.

** Electrolytes, calcium, magnesium, liver function tests and LDH.

**9. MEASUREMENT OF EFFECT**

For the purposes of this study, patients should be re-evaluated for response every 2 cycles. In addition to a baseline scan, confirmatory scans should also be obtained *not less than 4* weeks following initial documentation of objective response.

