**Subgroup B: DTIC pretreated**

These patients may have received a maximum of two prior lines of chemotherapy, and must have received DTIC or temozolomide.

All patients will be treated with Epothilone B analogue BMS 247550, 20 mg/m2 IV over 1 hour on days 1,8,15 of a 28 day cycle.

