## 2.1.1 Standard Therapy

In the first-line chemotherapy treatment of patients with stage IV disease, agents with reproducible activity against melanoma include DTIC, cisplatin, nitrosoureas and vinca alkaloids. DTIC is the most active single agent with response rates ranging from about 10% to 20%, and median response durations of 4 to 6 months (2). Although several recent studies using a combination of DTIC and other agents have shown increased response rates (see below), these combinations have not proven to be superior to single agent DTIC for the general population. Similarly, a Phase III study comparing temozolomide to DTIC showed no substantial improvement in survival or in other primary clinical endpoints (3).

A variety of combination chemotherapy regimens have produced response rates of 30% to 50% in single-institution Phase 2 trials. Two of the more active regimens were the 3-drug combination of cisplatin/vinblastine/DTIC (CVD) (4) and the 4-drug combination of cisplatin/DTIC/BCNU/tamoxifen (CDBT) (5). However, a randomized multi-institutional trial comparing CVD to DTIC alone, the CVD arm was not significantly superior in response rate, response duration, or survival (6). In a recent update of this trial, that encompassed approximately 150 patients, the CVD arm produced a 19% response rate compared to 14% for DTIC alone with no difference in either response duration or survival. A randomized, Phase 3 trial (EST 91-140) also demonstrated no significant survival benefit associated with CDBT relative to DTIC alone.

Several recent studies have indicated potential value for the addition of either interferon- or tamoxifen to DTIC (7-9). The actual benefit of the addition of interferon and/or tamoxifen to DTIC in patients with advanced melanoma was tested by the Eastern Cooperative Oncology Group (ECOG) in a large-scale, four-arm, Phase 3 trial (EST 3690). The overall response rate was 18% (range 12% to 21% for the 4 arms), median time to treatment failure was 2.6 months, and median survival was 9.1 months. There was no increase in objective response, increased duration of time to progression, or survival advantage attributable to the addition of interferon, tamoxifen, or both to DTIC. Based on this trial and the cumulative data from prior studies, there is no compelling evidence to support the addition of either interferon or tamoxifen to DTIC in this disease.

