**5.2 Dosing Delays / Dose Modifications**

Prior to retreatment, patients must have recovered the following organ function:

- absolute neutrophil count 1.0 x 109/l
- platelets 100 x 109/l
- total bilirubin within normal institutional limits
- AST (SGOT) / ALT (SGPT) 2.5 x upper limit of normal
- creatinine 1.5 x upper limit of normal
- other Grade 0-1

Any patient experiencing the relevant toxicities (cited below in section 5.2) after one dose reduction will be removed from the protocol.

Patients should be dose reduced to 16 mg/m2 IV (20% dose reduction) over 1 hour in the event of any of the following:

- grade 4 neutropenia 5 days
- febrile neutropenia
- grade 4 thrombocytopenia
- grade 3 non-hematological toxicity
- 1 week delay for recovery from any toxicity

No patients should have his / her dose re-escalated following dose reduction.

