**9.5 Time to Progression**

Time to progression is defined as the time from the first day of treatment with BMS 247550 until the first documentation of disease progression.

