**11. STATISTICAL CONSIDERATIONS**

**11.1 Endpoints**

Primary endpoint:

- Response rate (RR)

Secondary endpoints:

- Time to progression (TTP)
- Toxicity
- Correlative Data

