**11.4 Analysis of Secondary Endpoints**

Median time to progression will be described for each subgroup.

Related toxicities will be described.

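### Tumor assessments are counted in cycles, not in weeks from first dose, so dosing delays shift scan dates and with them the recorded time to progression

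*Protocol*

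**What the plan says.** Section 9 of the protocol states that "patients should be re-evaluated for response every 2 cycles". The study calendar agrees: tumor measurements appear only in the column for every second cycle. The Schema gives treatment "on days 1,8,15 of a 28 day cycle", so two undelayed cycles take 56 days. No passage expresses the interval in weeks from first dose or says whether the scan stays on its date when dosing slips.

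Dosing can slip. Section 5.2 opens with "Prior to retreatment, patients must have recovered the following organ function" and states no maximum wait. The same section lists "1 week delay for recovery from any toxicity" among the triggers for dose reduction (any comparison sign is not legible in the text at hand). It removes from the protocol a patient who has a listed toxicity again after one reduction.

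Under Section 9.5, TTP runs from the first day of treatment "until the first documentation of disease progression". Section 11.1 lists it as a secondary endpoint. Section 11.4 gives its whole analysis: "Median time to progression will be described for each subgroup".

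**The concern.** TTP is dated by when progression is seen, not by when it occurs. With scans on a cycle count, the date of seeing depends on how well the patient tolerates the drug. Two patients with the same tumor course can receive different TTP values because one had a dose held for a week.

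A second effect comes from the 8-week spacing itself. If progression is found only at scans, the recorded median falls on a scan date, and a range of true medians gives the same answer. Section 2.1.1 offers a figure for judging how coarse the grid is: in a four-arm phase 3 trial of DTIC-based treatment, "median time to treatment failure was 2.6 months". That value lies between the first and second scheduled scans.

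At stake is the meaning of the median TTP reported for each subgroup. The timing of a scan cannot be repaired at the analysis stage, so the first effect has to be dealt with in the protocol.

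**Working it through.** **The plan's own figures.** The protocol gives no design figure for TTP. Its only operating characteristics belong to the three-stage response-rate design. These were recomputed exactly, by convolving the binomial response counts stage by stage and stopping when cumulative responses are at or below the boundary:

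| Subgroup | Quantity | Stated | Recomputed |
|---|---|---|---|
| A (10% vs 25%; 0/11, 3/29, 7/50) | alpha | 0.10 | 0.0988 |
| | power | 0.90 | 0.902 |
| | early stop at 10% | 0.70 | 0.702 |
| B (5% vs 20%; 0/12, 1/25, 3/38) | alpha | 0.10 | 0.0952 |
| | power | 0.90 | 0.901 |
| | early stop at 5% | 0.72 | 0.716 |

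All agree. TTP enters none of these boundaries or error rates.

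**Inputs for the TTP check.**
- Scan interval: 2 × 28 = 56 days = 8 weeks = 56/30.44 = 1.84 months (Section 9 and Schema).
- Illustrative true median: 2.6 months = 2.6 × 30.44/7 = 11.31 weeks, about 79 days. The value is from Section 2.1.1. Using it as a true TTP median is an assumption.
- Assumed: exponential progression times, and detection only at scheduled scans.
- Proportion progressed by week t: F(t) = 1 − 0.5^(t/11.31).

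**Step 1, no delay.** Scans fall at weeks 8 and 16. F(8) = 0.388 and F(16) = 0.625. Half the patients are first recorded as progressed at week 16, so the recorded median is 112/30.44 = 3.68 months against a true 2.6. The difference is 1.08 months (3.68/2.6 = 1.42). Any true median between 1.84 and 3.68 months would also be recorded as 3.68. In simulated trials with a true 2.6, the sample median was exactly 3.68 in 82% of trials at n = 38 and in 88% at n = 50.

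**Step 2, one 1-week delay before the first scan in every patient.** Scans fall at weeks 9 and 17. F(9) = 0.424 and F(17) = 0.647. The recorded median is 17 weeks = 119/30.44 = 3.91 months.

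**Step 3, delays in some cycles only.** Let each cycle slip by 1 week with probability 0.25 (an assumption; the protocol gives no delay rate). Over two cycles, the chance of 0, 1 or 2 delays is 0.5625, 0.375 and 0.0625.
- Recorded as progressed after the first scan (weeks 8 to 10): 0.5625 × 0.388 + 0.375 × 0.424 + 0.0625 × 0.458 = 0.406.
- Added at week 16 (no delay in four cycles): 0.5625² × (0.625 − 0.388) = 0.075, total 0.481.
- Added at week 17 (one delay in four cycles): 0.211 × (0.647 − 0.388) + 0.211 × (0.647 − 0.424) = 0.102, total 0.583.

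The median is again 17 weeks, 3.91 months. With probability 0.5, simulation gives 4.14 months.

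**Step 4, direction.** A 14-day delay in every cycle puts the first scan at day 84, after the true median of day 79. More than half the patients are then recorded as progressed at that first scan, and the recorded median falls to 84/30.44 = 2.76 months. The effect of delay is therefore not monotone.

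**Step 5, detection between scans.** If 25% or 50% of progressions are found clinically when they occur, the undelayed recorded median is 3.68 or 3.56 months.

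**Step 6, what a calendar schedule alone achieves.** Scans held at weeks 8 and 16 remove the dependence on delay, but a true 2.6 is still recorded as 3.68. The grid effect needs a separate remedy.

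**The case against.** The case for leaving this alone has several parts.

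TTP is secondary, is only described, and has no test, threshold or comparator. That stands. A reader might infer that the trial would be unable to distinguish the drug from the course quoted in Section 2.1.1. The protocol plans no such comparison, and its decisions rest on response rate.

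The 2.6 months is a time to treatment failure on DTIC-based arms. It is not TTP, not a natural-history figure, and not a figure for pretreated patients. It is also an observed median from a trial whose assessment schedule is not given. That stands too, so the value serves here only to show scale. The 8-week interval is 71% of it (1.84/2.6).

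A reader might infer that every further delay lengthens TTP, or picture a 1-week delay in every cycle, which would put the median at 20 weeks. The documents support neither. Step 4 shows that the effect can reverse. Section 5.2 also limits repeated delays: a listed delay leads to dose reduction, and a further listed toxicity leads to removal.

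Progression can be documented between scans. A physical exam is scheduled before each next cycle, superficial lesions can be measured clinically, and any new lesion counts as progression. So the grid does not wholly determine the median, but step 5 shows the reduction is modest.

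Finally, the analysis method is commonly left to a statistical analysis plan, so its absence from the protocol is not a fault. The scan date is different: it is set by the protocol and cannot be recovered later.

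**Conclusion.** The point holds in a limited form. Scan dates follow cycles, so dosing delays move them, and modest delays generally push the recorded progression date later for the same tumor course. Under the stated assumptions, the shift from delay alone is from 3.68 to 3.91 months, either when every patient has one 1-week delay before the first scan or when a quarter of cycles slip by a week. The larger part of the overstatement, 2.6 recorded as 3.68 months, comes from the 8-week spacing and is present without any delay. Both sizes depend on exponential progression, on 2.6 months as an illustrative true median, and on detection mainly at scans. The delay frequency is assumed. The consequence is confined to the descriptive median TTP in each subgroup. The response-rate boundaries, error rates and early-stopping probabilities are unaffected. The change is worth making because it is nearly free and cannot be made after the data are collected.

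**What to change.** In Section 9 and the study calendar, schedule tumor assessments every 8 weeks from the first dose, within a window of a few days, regardless of treatment delays. This removes the dependence on tolerance and leaves the planned interval as it is.

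Calendar scans do not remove the grid effect. In Section 11.4, therefore, add the proportion progression-free at weeks 8 and 16, which is read directly at scan times. Add also an interval-censored median TTP beside the conventional one, taking each progression to lie between the last assessment without progression and the first that shows it.

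The costs are a sentence in Section 9, a calendar edit, a line in Section 11.4 and a small amount of analysis work. Some scans will no longer coincide with the start of a cycle, which is a minor inconvenience for sites and patients. The reported median TTP may look less favorable than it would under the present schedule.
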